### Measures

#### Anthropometric measures

Anthropometric data were measured using standard practices [39]. Weight was recorded to the nearest 0.1 kilograms using calibrated measurement scales (Salter). Height was measured using a stadiometer (Seca) to the nearest 0.1 cm. Waist circumference data was collected using a flexible non-elastic tape measure. The tape measure was placed around the participant's waist at the level of the umbilicus.

#### Fat mass, fat free mass and percent body fat

BIA was used to estimate fat mass, fat-free mass and percent body fat [40]. Prior to testing, participants were required to lie quietly in a supine position and were kept warm to ensure good circulation. The participant was instructed to lie with their legs slightly apart and hands resting next to the body palms down.

An alcohol wipe was used to remove excess oil and electrodes were placed on the right wrist between the two protruding bones, on the dorsal surface of the right hand 1 cm proximal to the middle knuckle, on the right ankle between the medial and lateral malleoli and on the dorsal surface of the right foot, 1 cm proximal to the metatarsal phalangeal joint of the second toe. The ImpediMed DF50 device was used. The yellow and red leads were connected to the electrodes on the participant's wrist and hand respectively, and the blue and black leads were connected to the electrodes on the participant's ankle and foot respectively. During testing, participants were required to lie still and not talk. Two separate readings were taken from each participant. Output values of impedance, phase, resistance and reactance were recorded.

For participants of Māori or Pacific descent, the Swinburn equation [41] was used to calculate fat mass, fat free mass and percent body fat. For participants who were not of either Māori or Pacific descent, the Lukaski equation [40] was used.

#### Cardiovascular fitness

Cardiovascular fitness was assessed using the 20 meter shuttle test, a standardized field assessment of cardiovascular fitness in children. This test requires participants to carry out a sequence of shuttle runs between two parallel lines positioned 20 meters apart. Each shuttle run is accompanied by a 'beep' audio signal which, when sounded, indicates that the run should have been completed. Those who do not manage this must stop the test and note the number of shuttle runs successfully accomplished and at what level. The timing begins relatively slowly but increases at intervals of approximately one minute. The beep test takes approximately 10 minutes to complete and the output can be used to predict maximal oxygen consumption (VO_2max_) in this age group [42].

#### Self-reported physical activity

Participants completed the Physical Activity Questionnaire for Children (PAQ-C), a validated self-report seven day recall physical activity measure, consisting of nine items that are used to calculate summary activity scores [43]. Items assess physical activity performed at school (physical education, recess, lunchtime), right after school, and at home (organized and recreational). Each PAQ-C statement is scored on a five-point scale with higher scores indicating higher activity levels. A mean score is obtained from each item. The final PAQ-C score is an average of these nine items.

#### Objectively-measured physical activity

Accelerometry was used to assess objectively-measured physical activity. The Actigraph (Model AM7164-2.2C) uniaxial (single-horizontal plane) accelerometer was used, which measures motion in the vertical plane, with movement outside of 'normal' motion being filtered electronically. Piezo-electric transducers and microprocessors detect movement which is converted to digital signals (movement counts).

Participants wore the accelerometer for seven consecutive days following each assessment. They were instructed to wear the monitor on their right hip in the mid-axilla line, during waking hours. Exceptions to this were any activities involving water (water sports, showering etc.), and any contact sports, in which wearing the accelerometer may cause injury to the participant, or damage the monitor. Participants also completed a daily log detailing the time the monitor was first put on and removed.

Because children tend to engage in physical activity in short duration bursts, a 10 second epoch was used and summed to give an activity count per minute [44]. The following cut-off points for METS were used to define light, moderate and vigorous levels of physical activity using the accelerometer: Light = 1.5 – 2.9 METS, moderate = 3 – 5.9 METS, vigorous ≥ 6 METS. For each valid recorded minute, the following equation was used to convert activity counts into equivalent MET values: MET = 2.757 + (0.0015*counts/min) - (0.08957*age) - (0.000038*counts/min*age) [45]. The obtained MET value was then converted into corresponding level of physical activity using the defined cut-off points. A valid accelerometer minute was defined as a recorded minute that does not fall into a sequence of ≥ 20 minutes of missing activity counts. A valid accelerometer day was defined as a recorded day that has a minimum of 600 valid minutes (i.e. 10 hours) [46]. All non-valid days and minutes will be removed from the accelerometer data before analysis. The average daily time spent in light/moderate/vigorous activities is calculated from valid minutes in valid days at each visit (a maximum of 7 days).

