### Participants

Children aged 10–14 years living in the greater metropolitan Auckland area, who are overweight (according to the Cole international cut-offs for child obesity) [37], play ≥ two hours of video games per week, and have no contraindications to perform physical activity are eligible to participate in the study. Participants are required to own a PlayStation^® ^2 or 3 gaming console but not the EyeToy™ or Dance Mat technology. Only one child per household is eligible to take part.

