### Outcomes

The primary outcome is change in BMI (kg/m^2^, z-score and centile) from baseline to 12 and 24 weeks. The secondary outcomes are change from baseline to 12 and 24 weeks on the following measures: Percent body fat (%), waist circumference (cm), physical fitness measured in VO_2max _(ml/kg/min), PAQ-C score, average daily time spent in light to vigorous activities (minutes), average daily time spent in active video games (minutes) and average daily time spent in non-active video games (minutes). Additional tertiary outcomes include change from baseline to 12 and 24 weeks on the following measures: Average daily time spent in light activities (minutes), moderate activities (minutes) and vigorous activities (minutes); psychological variables intention, self-efficacy, barrier efficacy, perceived competence, perceived enjoyment; and average daily total energy consumed from snacks (kJ).

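### As printed, the MET equation never falls below 1.5 METs for children up to about 14.03 years, so the secondary light-to-vigorous outcome is essentially valid wear time

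*Protocol article*

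**What the plan says.** All references are to the protocol article.

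- **Objectively-measured physical activity, conversion.** The equation is "MET = 2.757 + (0.0015*counts/min) - (0.08957*age) - (0.000038*counts/min*age"). It applies to all valid data: "For each valid recorded minute, the following equation was used to convert activity counts into equivalent MET values".
- **Same section, classification.** The bands are "Light = 1.5 – 2.9 METS, moderate = 3 – 5.9 METS, vigorous ≥ 6 METS", and "The obtained MET value was then converted into corresponding level of physical activity using the defined cut-off points". No sedentary band is named, and no count threshold sends low-count minutes elsewhere.
- **Same section, validity.** A valid minute is "a recorded minute that does not fall into a sequence of ≥ 20 minutes of missing activity counts". A valid day has "a minimum of 600 valid minutes (i.e. 10 hours"). Activity time is averaged over valid minutes in valid days.
- **Outcomes.** A secondary outcome is "average daily time spent in light to vigorous activities (minutes"). Light, moderate and vigorous time are each tertiary outcomes.
- **Participants.** "Children aged 10–14 years living in the greater metropolitan Auckland area" are eligible, subject to the other criteria. Statistical analysis gives age in years; neither section says whether decimals enter the equation.

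**The concern.** A measure of time in light or greater activity is informative only if some worn minutes can fall below light. If the equation's minimum is already at the lower limit of light, the three bands together take in all valid time, and their sum counts minutes worn, not minutes active.

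This matters for two reasons. Physical activity is a stated aim of the trial, and this is the only accelerometer outcome at secondary level; PAQ-C and the game-time logs are self-reported. The intervention also asks children to replace inactive play with active play, and that is the shift the sum is least able to show.

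**Working it through.** **Inputs.** The equation, the 1.5 and 3 MET limits and the validity rules come from Objectively-measured physical activity. The age range comes from Participants. The plan gives no figure of its own to reproduce. Write c for counts/min.

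**Step 1: value at zero counts and slope.** MET(0) = 2.757 − 0.08957 × age. Slope per count = 0.0015 − 0.000038 × age. Counts needed for 3 METs = (3 − MET(0)) / slope.

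| Age | MET at c = 0 | Slope per count | Counts/min for 3 METs |
|---|---|---|---|
| 10 | 1.861 | 0.001120 | 1017 |
| 11 | 1.772 | 0.001082 | 1135 |
| 12 | 1.682 | 0.001044 | 1262 |
| 13 | 1.593 | 0.001006 | 1399 |
| 14 | 1.503 | 0.000968 | 1546 |

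The slope is positive throughout, so zero counts gives the minimum. At each whole-year age in range that minimum is above 1.5.

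**Step 2: age at which the minimum reaches 1.5.** (2.757 − 1.5) / 0.08957 = 14.03 years.

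**Step 3: completed years 10–14.** Let V be valid minutes on a valid day (V ≥ 600) and M the minutes at 3 METs or more. No valid minute is below 1.5 METs, so light = V − M and light-to-vigorous = (V − M) + M = V. Tertiary light time contains all valid sedentary minutes.

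**Step 4: decimal age above 14.03.** Counts needed for 1.5 METs = (1.5 − MET(0)) / slope.

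- Age 14.5: MET(0) = 1.458; about 44 counts/min.
- Age 14.99: MET(0) = 1.414; about 92 counts/min.
- Age 15 (a child with a birthday during follow-up): MET(0) = 1.413; about 93 counts/min.

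For these children the outcome is valid time minus near-still minutes. If ages were uniform from 10.0 to 14.99 (an assumption), the share above the crossing age would be (15 − 14.0337) / 5 = 19%.

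**Step 5: response to a swap.** Suppose a child up to 14.03 years replaces 30 minutes of seated play with 30 minutes at 3 METs or more.

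- Seated minutes already valid: light falls by 30, M rises by 30, and the sum stays at V.
- Seated minutes removed as a run of 20 or more missing counts: the sum rises by up to 30. This requires that zeros be treated as missing, which the article does not say.

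The change is thus 0 in the first case and up to 30 in the second. The second gain comes from the validity filter and not from the MET classification.

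**The case against.** **Decimal age.** If age is entered with decimals, equality with wear time fails for children above about 14.03 years. This stands, and it limits the exact statement to completed years. It does not rescue the outcome: younger children still have no sedentary category, and the same stillness is scored differently by age.

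**The validity filter.** A reader might infer that the outcome cannot respond to the intervention at all, or that a 30-minute swap must score zero. The article does not support either, because the meaning of missing counts is left open (Step 5). For the same reason, a difference between arms need not be purely a difference in how long monitors were worn. Participants are unblinded, but nothing in the article indicates that wear would differ by arm.

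**Other activity measures.** A reader might infer that the physical activity question would be answered wrongly. That goes too far. PAQ-C is secondary, and moderate and vigorous time are tertiary. None depends on the 1.5-MET limit.

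**Children crossing 14.03 during follow-up.** Reclassification needs decimal age updated at each visit, which is not stated. Randomization makes it equally likely in both arms, so it would add noise; no bias between arms is shown.

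**An unseen analysis plan.** Wear-time adjustment may well be specified there, and its absence from the article is not a criticism. But the equation, cut-offs, validity rules and outcome are fixed in the article, and the fault lies in how they combine. With completed years, adjusting this outcome for valid wear time would adjust a quantity for itself.

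**A possible misprint.** The equation cannot be checked against its source here. If it is misprinted, the article still needs correcting.

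**Conclusion.** The point holds for the equation as printed. With age in completed years 10–14, light-to-vigorous time is exactly valid wear minutes per valid day, and light time includes all valid sedentary minutes. With decimal age this remains exact up to about 14.03 years; above that age the outcome also excludes near-still minutes.

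The conclusion assumes that the bands are contiguous, so that values between 2.9 and 3 or between 5.9 and 6 belong to one of them, and that METs are not rounded before classification. Rounding to one decimal would move the crossing age to (2.757 − 1.45) / 0.08957 = 14.59 years and leave the conclusion otherwise intact.

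The damage is confined to one secondary outcome and tertiary light time. The primary BMI outcome, the sample size, PAQ-C, and moderate and vigorous time are unaffected.

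**What to change.** - Redefine the secondary accelerometer outcome as average daily minutes at 3 METs or more, which this equation does separate (about 1017 counts/min at age 10 to 1546 at age 14). This is the sum of two outcomes already listed. Mean counts per valid minute is an alternative.
- Adjust minutes-based accelerometer outcomes for valid wear time.
- If light time stays as a tertiary outcome, set its lower limit by a pre-specified count cut-point, not by 1.5 METs from this equation.
- State whether age enters in completed or decimal years and whether it is updated at each visit. State also whether runs of zeros count as missing in the 20-minute rule.

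The cost is a change to the outcome definition and its programming, made before analysis. It uses the counts the monitors record and needs no extra measurement. The article does not show that data collection is complete, since it describes recruitment as still in progress, but the fix does not depend on that.

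### The printed MET equation scores motionless minutes as light activity at ages 10 to 14, and the non-wear rule does not say whether runs of zero counts are removed

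*Protocol article*

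**What the plan says.** All the processing rules are in the protocol article under Objectively-measured physical activity.

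- **Device.** "Piezo-electric transducers and microprocessors detect movement which is converted to digital signals (movement counts"). The text does not say what is stored when the monitor is still or has been taken off.
- **Wear.** Children wear the monitor "during waking hours" and take it off for water activities and contact sports. "Participants also completed a daily log detailing the time the monitor was first put on and removed".
- **Valid minute.** It is defined as "a recorded minute that does not fall into a sequence of ≥ 20 minutes of missing activity counts". The word *missing* is not defined, zero counts are not mentioned, and the log is not linked to the rule.
- **Valid day.** It is "a recorded day that has a minimum of 600 valid minutes (i.e. 10 hours").
- **Conversion.** Each valid minute goes through "MET = 2.757 + (0.0015*counts/min) - (0.08957*age) - (0.000038*counts/min*age") and is then classed as "Light = 1.5 – 2.9 METS, moderate = 3 – 5.9 METS, vigorous ≥ 6 METS". No class below light is named.

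Under Outcomes, average daily light-to-vigorous minutes is a secondary outcome. Light, moderate and vigorous minutes taken separately are tertiary outcomes. Under Participants, eligibility covers "Children aged 10–14 years living in the greater metropolitan Auckland area".

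**The concern.** Two steps in the data reduction interact.

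First, the non-wear rule depends on the word *missing*. If the device turns movement into counts, a monitor lying on a table would be expected to give a count of zero, which is a recorded value. Removal happens every day by design: at night, in water and during contact sports. An analyst who follows the sentence literally may keep that time as valid.

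Second, whatever is kept goes into an equation whose intercept, at these ages, already lies at or above the floor of the light band. A motionless minute is then counted as activity whether or not the monitor was worn.

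At stake is the meaning of the light-to-vigorous outcome. The Intervention section asks children to replace inactive gaming with active gaming. If still minutes already count as light, that substitution cannot change light-to-vigorous time, and a difference between arms would mainly reflect how much valid time was recorded.

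**Working it through.** **Inputs.** The equation, cut-offs, 20-minute rule and 600-minute threshold come from Objectively-measured physical activity. The age range comes from Participants. Wear time is not given, so it is assumed below and shown over a range.

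**The plan's own figure.** 600 / 60 = 10 hours, as stated.

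**Step 1: METs at zero counts.** With c = counts/min, the equation can be regrouped as

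MET = (2.757 − 0.08957 × age) + (0.0015 − 0.000038 × age) × c.

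At c = 0 only the first bracket remains. The second bracket is the slope. It is positive at every age here, so MET(0) is the lowest value a minute can take.

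| Age | MET at 0 counts | Slope per count | Counts/min at 3 METs |
|---|---|---|---|
| 10 | 1.861 | 0.001120 | 1,017 |
| 11 | 1.772 | 0.001082 | 1,135 |
| 12 | 1.682 | 0.001044 | 1,262 |
| 13 | 1.593 | 0.001006 | 1,399 |
| 14 | 1.503 | 0.000968 | 1,547 |

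The last column is (3 − MET(0)) / slope. At each whole-year age from 10 to 14, everything from complete stillness up to about 1,017 to 1,547 counts/min is classed as light, and no count value falls below light.

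**Step 2: where this stops.** MET(0) = 1.5 at age (2.757 − 1.5) / 0.08957 = 14.03. If age is entered as a decimal, older children fall below the floor at zero counts: 1.481 at 14.25, 1.458 at 14.5 and 1.413 at 15. The count needed to reach 1.5 METs is then about 20, 44 and 93 counts/min.

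**Step 3: effect on the outcome.** Up to age 14.03 every valid minute is at least light. Light-to-vigorous minutes per day therefore essentially equal valid minutes per day. Zero-count minutes give at most 1.861 METs, so they never enter the moderate or vigorous classes.

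**Step 4: how much the non-wear wording could matter.** Assume that the monitor stores a zero for each still minute over 24 hours and that the log is not used. The literal rule then leaves 24 × 60 = 1,440 valid minutes whatever the wear time. The zero-run reading is taken here to remove exactly the unworn time.

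| Assumed wear | Valid min, literal | Valid min, zero runs removed | Unworn min kept by literal rule | Day valid if zero runs removed? |
|---|---|---|---|---|
| 8 h | 1,440 | 480 | 960 | No |
| 13 h | 1,440 | 780 | 660 | Yes |
| 16 h | 1,440 | 960 | 480 | Yes |

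Under the same assumptions, 10 unworn hours (600 minutes) would meet the valid-day threshold by themselves.

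**Step 5: the charitable reading.** Suppose that *missing* means zero and that runs of 20 minutes or more are removed. Still worn minutes in shorter runs remain valid, and Step 1 scores them as light. Steps 1 to 3 therefore hold on either reading. Only Step 4 depends on the wording.

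**The case against.** The strongest reply is that *missing* is loose wording for minutes without counts. A 20-minute run length and a 600-minute minimum make ordinary sense as a non-wear screen based on zeros, and the literal reading would leave them with almost nothing to do. The sentence would also be correct as written if off-times in the log were blanked first. The article does not say what a removed monitor stores. It is a condensed account, and its Discussion says the pilot settled the data reduction protocols.

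Most of this stands. A reader might infer that the rule removes no non-wear at all, that every child scores 1,440 light-to-vigorous minutes a day, and that the arms cannot differ. The document does not support that. The inference needs zeros stored during removal, a meaning of *missing* that excludes them, 24-hour recording, no use of the log, and ages no higher than about 14.03. None of the first four is stated, and decimal ages would break the last for most 14-year-olds and for anyone turning 15 during follow-up. Nor is it a finding in itself that the article omits how the log is reconciled with the counts, since an article may leave that to a fuller document.

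The reply does not reach the equation and cut-offs. They are printed as operative rules, and with them a still minute is light at every whole-year age in the eligible range, however non-wear is found.

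**Conclusion.** The point holds in two parts of unequal strength.

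- **Firm.** With the printed equation and cut-offs, zero counts give 1.86 to 1.50 METs at ages 10 to 14, so each still valid minute is classed as light. The secondary light-to-vigorous outcome largely measures valid recorded time, and the tertiary light-minutes outcome is inflated. This rests only on the printed formula and on age being no higher than about 14.03.
- **Conditional.** The non-wear wording is ambiguous. If removed monitors store zeros and the sentence is applied literally, unworn time is kept (about 480 to 960 minutes a day for 16 down to 8 hours of assumed wear over a 24-hour record) and the valid-day test is weakened. The document does not establish that this happens.

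Moderate and vigorous minutes are not directly inflated, although a weakened valid-day test could change which days enter their averages. Change in BMI, the primary outcome, is unaffected. The rules should be corrected before the accelerometer outcomes are analysed.

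**What to change.** 1. Define non-wear as a run of at least 20 minutes of zero counts, and cross-check it against the on and off times in the log already collected. The check also helps to separate long quiet periods while worn from removal.
2. Apply the existing 600-minute test to the minutes that remain.
3. Class zero-count (sedentary) worn minutes below light before computing the light and light-to-vigorous outcomes, for example with a count-based lower bound for light activity, stated and justified in advance. Changing *missing* to *zero* alone would not repair these outcomes.
4. State whether age enters the equation in whole or decimal years, because the classification of stillness changes at about 14.03.

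The cost is a few sentences in the data-reduction rules and reprocessing of existing data. No new data are needed. Fewer days are likely to count as valid, and light minutes will fall.

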### Statistical analysis

Statistical analyses will be performed using SAS version 9.1.3 (SAS Institute Inc. Cary NC) and R version 2.8.1 (R Foundations for Statistical Computing). All statistical tests will be two-tailed and a 5% significance level maintained throughout the analyses. All treatment evaluations will be performed on the principle of Intention to Treat (ITT). Repeated measures analysis using the mixed model will be carried out to evaluate the effect of intervention on change from baseline measures at 12 and 24 weeks, adjusting for baseline outcome measure, age (in years), sex (male/female), and ethnicity (Māori/Pacific/nMnP). With roughly equal number of Māori, Pacific and non-Māori non-Pacific participants, appropriate sub-group analysis will be carried out for each ethnicity if there is a significant overall treatment effect.

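### Accelerometer minutes are not scaled or adjusted for worn time, so a wear difference between unblinded arms could pass for an effect: modest for moderate and vigorous minutes, near total for light-to-vigorous minutes

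*Protocol article*

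**What the plan says.** All references are to the protocol article.

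- **Objectively-measured physical activity, wear instruction.** "They were instructed to wear the monitor on their right hip in the mid-axilla line, during waking hours". The length of a waking day is not given. The monitor comes off for some activities: "Exceptions to this were any activities involving water (water sports, showering etc.), and any contact sports". Wear is also recorded: "Participants also completed a daily log detailing the time the monitor was first put on and removed". No use of that log in the analysis is described.
- **Same section, data reduction.** "A valid accelerometer day was defined as a recorded day that has a minimum of 600 valid minutes (i.e. 10 hours"). There is no upper cap. Minutes and days that are not valid are dropped, and the daily average is then formed: "The average daily time spent in light/moderate/vigorous activities is calculated from valid minutes in valid days at each visit (a maximum of 7 days"). Counts are converted to METs by an equation in counts and age, and light activity starts at 1.5 METs.
- **Outcomes.** One secondary outcome is "average daily time spent in light to vigorous activities (minutes"). Light, moderate and vigorous minutes taken separately are tertiary.
- **Statistical analysis.** A repeated measures mixed model on change from baseline, "adjusting for baseline outcome measure, age (in years), sex (male/female), and ethnicity". Wear time is not in the list.
- **Procedure.** Neither participants nor the staff who assess outcomes are blinded.

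**The concern.** Activity is recorded only while the monitor is worn. A day with 600 valid minutes and a day with 900 each count as one day, so a child who wears the monitor longer accumulates more minutes at the same level of activity. Neither the definition of the outcome nor the model allows for this.

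Two consequences follow. First, if wear at 12 or 24 weeks differs between arms, the difference passes into the estimated effect. Adjusting for the baseline outcome does not remove a difference that arises after randomisation. Children and staff know the allocation, so such a difference is possible. Second, even with equal wear in the arms, variation in wear between children and visits adds variance that has nothing to do with behaviour.

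One secondary and three tertiary outcomes are exposed. Physical activity is among the stated aims, and a positive result on these outcomes could not be told apart from a difference in wear. The primary outcome, BMI, is unaffected.

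**Working it through.** The article gives no figure for expected wear or waking hours, so there is no stated number to reproduce here. Inputs from the article: the 600-minute threshold, the MET equation, the light cut-off of 1.5, and ages 10 to 14. Everything marked *assumed* is not in the article.

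**1. Light-to-vigorous minutes (needs no assumed activity share).** At zero counts the equation reduces to MET = 2.757 − 0.08957 × age.

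| Age (years) | MET at zero counts |
|---|---|
| 10 | 1.861 |
| 11 | 1.772 |
| 12 | 1.682 |
| 13 | 1.593 |
| 14 | 1.503 |

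All exceed 1.5, and METs rise with counts, so with age in whole years every valid minute scores at least light. With decimal age this fails only above (2.757 − 1.5)/0.08957 = 14.03 years. At 14.99 years zero counts give 1.414 MET, and about 92 counts/min reach 1.5. Light-to-vigorous minutes are therefore essentially valid worn minutes, and an arm difference in wear of 30 minutes appears as about 30 min/day. That equals the 30 minutes of daily play in the trial's hypothesis (Background).

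**2. Moderate-to-vigorous minutes, shift between arms with no true effect.** Shift = share of wear × wear difference. With a share of 8% (*assumed*): 0.08 × 30 = 2.4 min/day. With 60 min/day in a 13-hour mean wear (*assumed* instead): 60 × 30/780 = 2.3 min/day.

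**3. Moderate-to-vigorous minutes, added noise.** Let the share S have mean 0.08 and SD 0.025, and let wear W have mean 780 minutes, independent of S (all *assumed*). Then

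Var(SW) = SD(S)² × (mean(W)² + SD(W)²) + mean(S)² × SD(W)²,

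compared with SD(S)² × 780² = 380.25 when every child wears the monitor for 780 minutes.

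- Wear SD 60: (0.000625 × 612,000 + 0.0064 × 3,600)/380.25 = (382.50 + 23.04)/380.25 = 1.07.
- Wear SD 90: (385.31 + 51.84)/380.25 = 1.15, or 1.14 when wear is clipped to 600–1,000 minutes.
- Wear SD 120: clipping matters more here. It reduces the SD to about 109, and the ratio is 1.23.

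These ratios are for one visit's measurement across children. They are not ratios for the baseline-adjusted change.

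**4. Understatement for one child at exactly 600 minutes.** Understatement = 1 − 10/H for a waking day of H hours (*assumed*), with activity proportional to time.

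| Waking day (h) | Understatement |
|---|---|
| 11 | 9.1% |
| 12 | 16.7% |
| 13 | 23.1% |
| 14 | 28.6% |
| 15 | 33.3% |
| 16 | 37.5% |

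**5. Does dividing by worn time work?** For moderate and vigorous minutes, yes: wear cancels if unworn time is as active as worn time. For light-to-vigorous minutes, step 1 makes the ratio about 100% for nearly every child. Multiplied by a fixed reference day, it is nearly the same constant in both arms.

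**The case against.** Three objections carry weight.

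*The analysis plan is not shown.* A wear covariate, wear reported by arm, or a sensitivity analysis may well be in it. That is fair, and the statement that nothing adjusts for wear holds for this article only. But the article does not leave the matter open: it defines how the daily average is formed and lists the adjusters. An analysis plan that dealt with wear in the main analysis would have to depart from or add to both.

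*Absolute minutes per valid day is a legitimate measure, and the 600-minute rule already gives some control.* This is true, but control from below only. The rule sets a floor and leaves wear free to vary above it.

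*Standardising has its own weakness.* It assumes that unworn time resembles worn time, which is doubtful for the water and contact sports during which the monitor is removed. This stands as a limitation of the remedy and is a reason to keep the raw minutes alongside.

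Two stronger readings are tempting and are not supported. A reader might infer that activity in this trial will be understated by a quarter or a third. That applies only to a child at exactly the minimum on every valid day, under an assumed waking day of about 13 to 15 hours. Understatement common to both arms is also no bias towards an effect; it shrinks the contrast in proportion. A reader might also infer that the arms will differ in wear. Lack of blinding makes this possible, but nothing in the article shows it.

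**Conclusion.** The point holds as a conditional one. The stated outcome and model let a wear difference between arms pass into the activity estimates, and variation in wear adds noise.

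- **Moderate and vigorous minutes (tertiary): modest.** About 2.4 min/day per 30 minutes of arm difference in wear, and a variance ratio of about 1.07 to 1.23. Both rest on the assumed 8% share, and the ratio also on a wear SD of 60 to 120 minutes.
- **Light-to-vigorous minutes (secondary): near total.** A 30-minute wear difference gives about 30 minutes. This rests on the article's own equation and cut-off, with an exception only for children older than about 14.03 years if decimal age is used.
- **Understatement for a single child: 9% to 38% at worst,** for assumed waking days of 11 to 16 hours. It is not in itself a bias between arms.

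This should be changed before the accelerometer outcomes are analysed. The BMI result does not depend on it.

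**What to change.** 1. For moderate and for vigorous activity, take minutes in the band over valid days at each visit, divide by valid minutes over the same days, and multiply by one fixed reference day (for example the trial's pooled mean valid minutes per day). Use this as the main analysis.
2. Report mean valid minutes per day by arm and visit for all accelerometer outcomes.
3. Keep the unstandardised minutes as a sensitivity analysis.
4. Reconcile the light cut-off with the MET equation first, and only then apply the same standardisation to the light and light-to-vigorous outcomes. Done in the other order, the standardised light-to-vigorous outcome is nearly constant and carries almost no information.
5. State the assumption that unworn time resembles worn time, and that it is weakest for water and contact sports.

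The valid-minute and valid-day rules can stay. For items 1 to 3 and 5 the cost is analysis-plan wording and a few lines of code, since valid minutes are already computed and no new data are needed. Item 4 needs a decision on the cut-off or the equation, preferably made without sight of results by arm.
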